## 5.2 Secondary objectives and research questions

Secondary objective 1: Examine effect of ImTeCHO intervention in the form of job aid to ASHA and ANM to increase coverage of care among complicated maternal, newborn and child cases by facilitating referral to a health facility and managing at home for those cases that unable to get referred in tribal areas of Gujarat.

Secondary research question 1: Can ImTeCHO intervention in the form of job-aid to ASHAs and ANM increase coverage of care among complicated maternal, newborn and child cases in tribal areas of Gujarat?

Complete list of set of indicators for secondary objective 1 can be found in Appendix 1.

Secondary Objective 2: Examine effect of ImTeCHO intervention in the form of a job aid to medical officers and PHC staff to improve support and supervision of ASHAs.

Secondary research question 2: Can ImTeCHO intervention in the form of a job aid to medical officers and PHC staff improve support and supervision of ASHAs?

- Proportion of ASHAs whose performance was reviewed by mHealth facilitator (more about mHealth facilitator in section 10.2) over a phone call per month
- Proportion and number of ASHAs who were contacted by mHealth facilitator (mostly through phone) every month for non-adherence to intervention
- Proportion of ASHAs who were visited in field by ImTeCHO facilitator for quality improvement
- Proportion of PHC meetings when [data from] ImTeCHO was used at least once for supervision by PHC staff
- Medical officer’s login and task completion rate
- Average number of phone call by SEWA Rural’s ImTeCHO facilitator per ASHA per month towards providing support
- Proportion of beneficiaries with high risk complications who received guidance from SEWA Rural’s helpline
- Average number of phone call by SEWA Rural’s helpline per ASHA per month towards providing guidance for morbidity management
- Average number of motivational announcements sent by SEWA Rural to ASHAs per month
- Average amount of extra incentives paid by SEWA Rural per ASHA per month

Secondary objective 3: Examine process indicators to understand processes and level of adherence to intervention.

Selected process indicators are listed below and complete list of process indicators are given in Appendix 1. The process indicators will be measured for intervention area only. Please refer to Figure 2 and 2 to see conceptual frameworks which were used to identify process indicators.

| **Sr no** | **Process indicators** |

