# 12 Measurement of outcomes and follow up

**Table 11 Measurement of outcomes**

| **What** | **Where** | **When** | **How** | **By Who** |
| --- | --- | --- | --- | --- |
| Coverage of proven maternal and newborn interventions, coverage of care among complicated maternal and newborn cases | At household level in community | 2 times: Pre-intervention (baseline), Post-intervention (end line) | Household survey as reported by mothers of infants age 1 to 3 months* | Data collection team |
| Coverage of proven young infant health interventions, coverage of care among complicated young infant cases | At household level in community | 2 times: Pre-intervention (baseline), Post-intervention (end line) | Household survey as reported by mothers of infants age 1 to 3 months | Data collection team |
| Adherence to intervention and Support and supervision received by ASHAs | From ImTeCHO program data (online) | Post-intervention (end line) | From web interface & log of ImTeCHO facilitator | Investigators |

* Mothers of infant age 6 to 8 months will be surveyed at baseline

*Data collection for all research questions*

Household surveys will be used for assessing set of indicators for primary objective, secondary objective-1 and secondary objective-4. The household survey tools is based on draft tool for district level health and facility survey (DLFHS-4) which is available online[[48]](#footnote-49). The survey tools are included in Appendix 2. Respondents will be

- For maternal, and newborn health interventions: All woman who are native of study village and is mother of an infant who is one to four months old at the time of survey will be considered as respondents for evaluation. All native women who resided most of the time (at least five months) in study cluster during antenatal period will be included. All women must be in the study cluster at the time of birth in case of home deliveries and in case of institutional deliveries if the she went to hospital from study cluster and came back to same study cluster immediately after delivery, and who provided consent for the evaluation will be included. All women who resided in study cluster for most of time during first month after delivery will be included. Women whose infant died before the survey will be excluded. Respondents will be identified through ongoing pregnancy and mortality surveillance which described later in this section.

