- For child health interventions: All adult woman who are native of study village and is mother of an infant who is six to eight months old at the time of survey will be considered as respondents for evaluation. Women whose infant died before the survey will be excluded.
- For indicators reflecting supervision and support (secondary research question 2 and 3) received by ASHAs in the intervention area, program data will be used from the ImTeCHO web interface and documentation of mHealth facilitators.

All pregnancy registrations, its outcomes, any newborn and infant deaths in all clusters throughout the study period will be counted as part of ongoing pregnancy and mortality surveillance. For that, outcome of all pregnancies will be determined to ensure complete counting of all newborn deaths. This will be done by data collection team by conducting house to house survey of whole study area on regular basis. All live births to woman who are native of study village will included irrespective of place of the birth.

*Follow up*

All new pregnant women and their neonates will be enrolled through ongoing pregnancy and mortality surveillance described above. Each pregnant woman and neonate will be followed up to one year after pregnancy outcome in both arms unless the woman or neonate dies or family migrates out of study area. All clusters and ASHAs will be followed throughout the study by the team of data collectors and investigators.

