## 15.4 Analysis plan

Data cleaning will be done using various relational checks and it will locked before analysis. Data analysis will be done as per the statistical analysis plan. Primary analysis will be intention to treat and secondary analysis would be per protocol. Data will be analysed taking tin to account cluster randomization. Analysis would be done at various levels i.e. at ASHA level, PHC level, subcenter level and at the beneficiary level. In the analysis at ASHA/subcenter/PHC level, cluster would be the PHC while for analysi at beneficiary level; outcomes would be considered correlated within the PHC in block and among the beneficiary under a fiven ASHA. Before comparing the primary and secondary outcomes at the ASHA or at the beneficiary level, both cluster level and the unit of analysis level characteristics would be compared. In case of any imbalance in any of the characteristics at cluster or at the beneficiary level, both cluster level and the unit of analysis level characteristics would be compared. In case of any imbalance in any of the characteristics at cluster or at the beneficiary level, adjustments will be done using Generalized Estimating Equation approach. Categorical variables will be summarized using frequency (5) and quantitative variables will be summarized at mean/median and SD/IQR, as appropriate. For each of primary and secondary outcomes, effect size (95% confidence interval, after adjustment if required, would be computed. STATA 13.0 will be used for data analysis. Results will be presented as per statistical analysis plan.

s

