# 17. Ethical and safety considerations

## 17.1 Areas of risk and potential solution

1. Data collection team might come across other morbidities among respondents. Patients will be referred to hospital irrespective of intervention or control cluster. Referred individuals will be given choice to go to SEWA Rural hospital which is providing outpatient and inpatient care to local community for more than 3 decades. 60% of outpatient and 80% inpatient care at SEWA Rural is provided free, if patient is non-affording.
2. An information sheet will be prepared in vernacular language having details regarding goals of the study along with potential risks and benefits to the participants and society. The data-collectors will give and explain information sheet to all the participants and address any questions. A written consent will be obtained from all consenting participants.
3. All personally-identifiable information will be removed and unique-number will be assigned to participants. Only principal investigators will have access to data linking personally-identifiable information with unique-number. The database will be protected by a password.
4. Privacy during data collection from ASHA and confidentiality of collected data will be strictly enforced to protect them from any harm from their supervisors (medical-officers etc) for revealing uncomfortable information regarding supervision and support.
5. Confidentiality of medical information to be recorded and transmitted using mobile-phone technology will be strictly enforced. All sensitive data will be codified and encrypted. Firewall will be used. The web-interface will be protected by password. The database server will be installed at a Tier 1 high security data-center.
6. Individual medical information will be collected using mobile phone and will be stored on server. This raises a concern regarding confidentiality of medical information. The proposed application shall contain medical information of individuals and hence demands high levels of data security. In view of this, the application shall accept, transmit, process and store data using prudent security and data encryption practices as described below.
   - Any data that is transmitted using GPRS from the Mobile Phone to the server and vice versa shall be encrypted. In addition, the data shall also be codified before encryption to provide an additional layer of obfuscation.

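### Secondary objective 2 asks for an effect on ASHA supervision, but all ten indicators listed for it come from the intervention arm only, so no effect can be estimated

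*Protocol*

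**What the plan says.** Section 5.2 frames secondary objective 2 in causal terms, as the effect of ImTeCHO in the form of a "job aid to medical officers and PHC staff to improve support and supervision of ASHAs". The matching research question is "Can ImTeCHO intervention in the form of a job aid to medical officers and PHC staff improve support and supervision of ASHAs". Ten indicators follow directly in the text.

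Section 12 fixes where the data come from: "For indicators reflecting supervision and support (secondary research question 2 and 3) received by ASHAs in the intervention area, program data will be used", namely the ImTeCHO web interface and the facilitators' own records. The row of Table 11 for adherence and for support and supervision gives source and timing as "From ImTeCHO program data (online) | Post-intervention (end line"). The surveys that run in both arms are assigned elsewhere: "Household surveys will be used for assessing set of indicators for primary objective, secondary objective-1 and secondary objective-4".

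Section 15.4 then sets a general rule: "For each of primary and secondary outcomes, effect size (95% confidence interval, after adjustment if required, would be computed". The summary in Section 1 repeats it.

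**The concern.** A question about whether an intervention improves something needs a comparison, with the control arm or at least with the period before. The indicators under objective 2 offer neither. They are produced by the intervention itself and would be zero or undefined wherever ImTeCHO does not run.

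Two things follow. The effect-size rule cannot be applied to these items as written. And if delivery counts are reported under an objective that speaks of an effect, a reader may take evidence that the programme was delivered as evidence that supervision got better. This matters because Section 1 names better supervision through the web interface as one of the three ways in which the intervention will be evaluated, and Section 18.2 intends the results to inform scale-up.

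**Working it through.** No sample size, power or error rate is attached to objective 2, so the check is a comparison of passages and a count.

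**Step 1. Classify the ten indicators in Section 5.2.** The control area receives usual services (Section 11) without mHealth tools (Section 17.2).

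| No. | Indicator (paraphrased) | Whose activity it counts | Control-arm data planned | Baseline data planned |
|---|---|---|---|---|
| 1 | Monthly performance review call | SEWA Rural facilitator | No | No |
| 2 | Contact because of non-adherence | SEWA Rural facilitator | No | No |
| 3 | Field visit for quality | SEWA Rural facilitator | No | No |
| 4 | ImTeCHO data used at PHC meetings | PHC staff | No | No |
| 5 | Login and task completion | Medical officer | No | No |
| 6 | Support calls per ASHA | SEWA Rural facilitator | No | No |
| 7 | High-risk cases given guidance | SEWA Rural helpline | No | No |
| 8 | Helpline calls per ASHA | SEWA Rural helpline | No | No |
| 9 | Motivational announcements | SEWA Rural | No | No |
| 10 | Extra incentives paid | SEWA Rural | No | No |

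**Step 2. Count.** Indicators listed: 10. With control-arm data: 0. With baseline data: 0. Estimable between-arm effects: 0. Estimable before-after effects: 0.

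**Step 3. See whether another data source fills the gap.**
- The household surveys serve the primary objective and secondary objectives 1 and 4, not objective 2 (Section 12).
- Section 17.1 refers to gathering information from ASHAs about supervision: "Privacy during data collection from ASHA and confidentiality of collected data will be strictly enforced". Section 12 and Table 11 define no such instrument, arm or time point.
- Table 12 of Section 13.1.2 lists PHC staff of both areas for training in the web interface. That sits badly with Sections 11 and 17.2, and it does not alter Section 12, which limits the supervision data to the intervention area.

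**Step 4. Ask whether setting control values to zero would rescue the comparison.** It would not. The difference would equal the intervention-arm value and would only restate that the programme was delivered.

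**Step 5. Compare the indicators with the wording of the objective.** The objective names medical officers and PHC staff. Indicators 4 and 5 concern them; the other 10 − 2 = 8 count SEWA Rural's own staff, messages or payments. Indicator 2 may even rise when delivery goes badly, so a higher value does not clearly mean better supervision.

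**Step 6. Contrast with objective 3.** Section 5.2 words objective 3 as understanding processes and adherence, and says openly that its process indicators are limited to the intervention area. Objective 2 rests on the same kind of data but keeps the language of an effect.

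**The case against.** The strongest reply is that the protocol already discloses the limit. Section 12 groups questions 2 and 3 under intervention-area programme data, and Table 11 puts supervision in the same row as adherence, so objective 2 could be read as implementation monitoring with one loosely chosen word. The rule in Section 15.4 speaks of outcomes while Section 5.2 lists indicators, and it may have been meant only for measures taken in both arms. Section 15.4 also defers to a statistical analysis plan. Appendices 1 and 2 are not shown and might hold more.

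Part of this stands. The finding should be confined to the ten listed indicators. Nothing in the protocol says that a control value will be imputed or a causal claim made, so misreporting is a risk and not a stated intention. No power calculation or primary analysis depends on objective 2.

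The rest does not remove the problem. An analysis plan cannot supply control data that are not collected. Section 5.2 points to Appendix 1 for objectives 1, 3 and 4 but not for objective 2, and Section 12 fixes the source for question 2 whatever the appendix contains. Table 11 presents support and supervision under a title about measuring outcomes, so the effect-size rule can fairly be read as covering it. That the rule taken literally would also fail for objective 3 is a further reason to qualify it.

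**Conclusion.** The concern holds. As written, objective 2 asks a causal question that its ten listed indicators cannot answer, and the effect-size rule of Sections 1 and 15.4 cannot be applied to any of them: 0 of 10 have a comparator. The conclusion rests on two readings of the text: that Section 12 governs the data source for research question 2, and that the control area runs without ImTeCHO. The primary outcomes and secondary objectives 1 and 4, which rest on the household surveys, are not affected. The matter is worth correcting because it changes what the trial may claim about supervision, and the correction is cheap.

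**What to change.** 1. Restate objective 2 and its research question descriptively, as the amount and type of support delivered to ASHAs in the intervention arm.
2. In Sections 1 and 15.4, limit the effect-size sentence to secondary outcomes measured in both arms, and say that the indicators for objectives 2 and 3 will be summarised descriptively.
3. Only if an effect on supervision is wanted, put a few arm-neutral items to ASHAs in both arms at endline, for example supervisory contacts in the last month, incentive paid on time, and stock-outs. The last two already exist as process indicators 3.3 and 3.2 under objective 3, for the intervention area only. Section 12 should then define the instrument, the arms and the timing, and be aligned with the ASHA data collection mentioned in Section 17.1.

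Items 1 and 2 cost only rewording. Item 3 needs a short questionnaire in both arms. Section 12 already has data collectors following all ASHAs, so the added fieldwork is modest, but the answers would be self-reported and unblinded, and would have no baseline unless one is added.

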## 5.3 Summary of participants, intervention, comparator and outcomes (PICO)

**Table 7: Summary of participants, intervention, comparator and outcomes (PICO)**

|  | **PICO components** | **Brief description** |
| --- | --- | --- |
| 1 | **Participants (complete description to follow in Section 9)** | ASHAs, ASHA facilitators, ANMs, Medical officers, PHC support staff, mHealth facilitators, help line, pregnant women and mothers of infants |
| 2 | **Intervention (complete description to follow in Section 10)** | *ASHA level:* mobile phone as job-aid to increase coverage of MNCH interventions. Job-aid tools that will be used are checklist, reminder, scheduling, videos, and algorithms to promote healthy behaviors.  *ASHA, ANM level:* Mobile phone as job-aid to facilitate care to complicated cases. This will include use of mobile phone as diagnostic aid, facilitate referral by calling emergency transport, send notification to ANM, and obtain management guidelines based on algorithms for those cases that are unable to go to health facility along with reminders to revisit complicated cases.  *Medical officer, ANMs and PHC staff including ASHA facilitators:* Web interface and mobile phone application to provide timely information to medical officer for monitoring and supporting maternal, newborn and child health program. Some of the features on web interface will include daily checklist to track complicated cases, weekly and monthly performance reports, reminders to pay incentives, incentive and supply management and ongoing surveillance data.  mHealth facilitator: This person, from SEWA Rural, will be first contact for ASHAs and PHC staff to report and solve any problem with the ImTeCHO mobile phone/web application and other related issues. The mHealth facilitators will monitor adherence to the intervention through use of set of process indicators. The mHealth facilitator would visit ASHAs in field to solve any technology issues and visit beneficiaries along with ASHAs for ongoing training/supervision/motivation. This person will not be involved in patient care and will not get in existing working arrangement within the govt. This person will facilitate use of ImTeCHO in government primary health care system only.  Help line: A counselor from SEWA Rural would provide help line services over phone. The help line would proactively contact and counsel all beneficiaries and ASHAs (ANMs and medical officers, if needed) to provide guidance for management of complications, including ensuring referral. ASHAs will be given help line number so that they can contact in case of any help required. |
| **3** | **Comparator (complete description to follow in Section 11)** | Usual practice in control area where current level of services provided by the government and other agencies will continue. |
| **4** | **Outcome** | - Improve proportion of neonates/mothers who received at least two postnatal home visits within first week of delivery by ASHA from 46% to 66% - Improve MACCI from 36% to 51% |

# 6. Study design

## 6.1 Design

This will be a two arm, parallel, stratified cluster randomized trial in which unit of randomization will be a PHC. Stratification is required to ensure that prevalence of primary outcomes are similar in the intervention and control groups along with almost equal selection of PHCs from from the most backward Dediyapada block. Stratification will be also done to improve power and precision. The randomization will be done after baseline survey. Along with primary outcomes, randomization would help to balance cluster size across both groups. The allocation ratio will be 1:1. Stratified randomization will be done by a statistician at AIIMS not involved in implementation of intervention. The baseline variable to be used for stratification will be the primary outcome indicator MACCI. The PHCs in each of the two strata will be randomly allocated into to intervention and control group. The randomization will be done using software nQuery. Due to the nature of the community-based intervention, blinding will not be possible.

Assessed for inclusion: 26 clusters

Randomized: 22 clusters

Did not meet inclusion criteria: 4 clusters

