**Figure 5 Data flow process for household surveys**

Data collector visits household

Data entry in smart phone using electronic household survey tool

Sync data from smart phone to interim database at the end of the interview

Data administrator reviews all data within 2 days of data collection date

Clarify inaccuracies with data collector within one week of data collection date

Data cleaning to be done by investigator and data administrator

“Release” data in main data center

Prepare final file for analysis

Data collection team will identify respondents for household survey using information from ongoing pregnancy registration and mortality surveillance as described in section 12. The data-collection team will enter data into smart-phones which will be loaded with data-collection tool with in-built checks for missing data and logical inconsistency. Data will be uploaded to a central server using GPRS where it will store in mysql database. A data-administrator will check for any inaccuracies and it will be clarified during review-meeting with data-collectors.

5% of households will be randomly selected and re-interviewed by an independent quality-assurance team using a truncated questionnaire. Data will be re-validated in case of more than 15% differences in key metrics are found. Data cleaning will be done as part of the ongoing process of identification of inaccuracies in the data, and subsequent rectification based on field inputs by the data-administrator, as per established protocols for editing and cleaning the data. Only investigators will have access to raw and personally identifiable data which will be protected by password. Any edits in the raw data-base will be allowed only after completing a query form. Any corrected data will be red-flagged. A separate form will be filled to state nature (who, when, why) for data corrections. Final data-set will be created once all surveys and surveillance activities are completed.

A data-center will be established at head-quarters. Protocol will be established ensuring security of data center. Data will be backed up on regular basis.

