# 16. Quality assurance

## 16.1 For home surveys

Data collector will enter the data on a smart-mobile and a paper-based data collection tool. Regular checks with be done by quality assurance team to find any discrepancy between digital and paper records; such discrepancy will be clarified with data collector within 10 days Process indicators (forms per day, time taken to complete one form etc) will be put in place to track data collection. As described above, any inaccuracies will be dealt within one week of data collection; data collector might need to return to the source if inaccuracy can not be clarified off-site. A separate quality assurance team will re-interview 5% of households to check quality of data. Smart-phones will be GPS-enabled.

Protocols for data cleaning will be prepared. Protocols will be established for editing any data. Only investigators will have access to raw and personally identifiable data which will be protected by password. Any edits in raw data-base will be allowed only after completing a query form. Any corrected data will be red-flagged. A separate form will be filled to state nature (who, when, why) for data corrections. Procedures will be in place to transfer data files.

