## 16.4 General study implementation

This will be reviewed during once a month meeting at head-quarter to be attended by on-site investigators and mHealth facilitators. Progress of the implementation will be assessed against proposed timeline. These meetings will be a platform to address issues identified during implementation of the project.

Steering committee meeting will be organized every twelve months during which issues related to coordination among various stakeholders will be discussed. Schedule of all monitoring and logistic meeting is indicated Table 12. It should be noted that regular meetings similar to ASHA and ANM review meetings are expected to take place now (in absence of the study) as per the protocol from the Ministry of Health and Family WelfareError: Reference source not found.

**Table 12** Schedule of meetings for quality assurance

| Name of meeting | Goal of meeting | Location | Frequency | Attendees |
| --- | --- | --- | --- | --- |
| PHC meetings (control and intervention area) | Review and support ASHA activities | PHC | Monthly | ASHAs, ANMs, medical officer and PHC staff, mHF |
| Implementation review meeting | Review process indicators and implementation related issues | Chief District Health Officer Office | Quarterly | Investigators, medical officers |
| Data collection review meeting | Review data collection | Head quarter* | Monthly during data collection period | On-site investigators, data collectors |
| Steering committee meeting | Review implementation of intervention | Head quarter | Once every twelve months | Steering committee member, investigators |
| Data Safety and Monitoring Board meeting | Review issues related to data safety and monitor data | Head quarter | Once a year | DSMB member, investigators |

*Head quarter mean SEWA Rural main campus at Jhagadia

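### Section 6.1 rules out all blinding for a reason that covers only providers and families, and so leaves central cleaning, editing and analysis of mother-reported endline outcomes unmasked to arm

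*Protocol*

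**What the plan says.** Section 6.1 dismisses blinding in one unqualified sentence: "Due to the nature of the community-based intervention, blinding will not be possible". It exempts no role and no step.

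On the outcomes, section 12 states: "Household surveys will be used for assessing set of indicators for primary objective". Table 11 describes the source as "Household survey as reported by mothers of infants age 1 to 3 months".

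On data handling:
- Section 15.2 first gives a checking role to the data administrator: "A data-administrator will check for any inaccuracies and it will be clarified during review-meeting with data-collectors".
- The data-flow figure in the same section then lists: "Data cleaning to be done by investigator and data administrator".
- Section 16.1 restricts access: "Only investigators will have access to raw and personally identifiable data which will be protected by password".

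On overlapping roles, section 16.4 has implementation reviewed at a "once a month meeting at head-quarter to be attended by on-site investigators and mHealth facilitators". Its meeting table also puts on-site investigators at the monthly data collection review with the data collectors. Section 12 adds: "All clusters and ASHAs will be followed throughout the study by the team of data collectors and investigators".

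Sections 15.2 and 16.1 set controls on edits: a query form, red-flagging, a record of who corrected what and why, and re-interview of 5% of households by an independent team. Section 15.4 locks the data before analysis. Section 17.1 replaces personal identifiers with a unique number.

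**The concern.** The nature of the intervention prevents masking of ASHAs, PHC staff and families. It does not prevent the people who review, edit and analyse survey records centrally from working on files in which the PHC, the block and the arm are coded. The protocol draws no such distinction.

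The first primary outcome, and five of the nine MACCI components, are mothers' reports of contact with the ASHA: whether and when she visited, whether care was sought from her, whether she supplied ORS. Small arm-related differences in how doubtful answers are queried or corrected go straight into the between-arm difference. Intention-to-treat analysis and allowance for clustering do not remove them. Because randomisation follows the baseline survey, knowledge of arm can affect only the endline data, so the baseline measurement neither shares nor reveals such a bias.

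**Working it through.** **Step 1. Set the passages side by side.**
- The reason in 6.1 concerns how the intervention is delivered. The steps in 15.2 and 16.1 take place after the interview, on a central database. The reason does not reach them.
- On-site investigators attend implementation meetings (16.4) and data collection reviews (16.4). Investigators share in cleaning (15.2) and alone have raw identifiable data (16.1). That cleaners can tell the arm is an inference from these roles and from the absence of any masking; the text does not state it.
- The controls on edits record changes; none conceals arm. The unique number in 17.1 replaces personal identifiers, and nothing says that PHC or arm is coded. The lock in 15.4 comes after the cleaning.
- The re-interview triggers re-validation only when key metrics differ by more than 15% (15.2), and no comparison by arm is stated.

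**Step 2. Postnatal-visit outcome, under an assumed shift.** The protocol gives no rate of edits or misreports, so 5-10% is an assumption.

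Inputs: control proportion 0.46, 22 ASHAs per PHC (Table 9), 11 PHCs per arm, ICC 0.02 (section 8).
- Share answering 'no': 1 − 0.46 = 0.54.
- Shift: 0.54 × 0.05 = 0.027; 0.54 × 0.10 = 0.054. A true 46% is recorded as 48.7-51.4%, against a 20-point target. This changes 2.7-5.4% of the arm's records, below the 15% trigger if that is read as a share of records.
- Design effect: 1 + 21 × 0.02 = 1.42. ASHAs per arm: 11 × 22 = 242.
- SE of the difference: √(2 × 0.46 × 0.54 × 1.42 / 242) = 0.054.
- Shift of 0.5 SE: P(Z > 1.46) + P(Z < −2.46) = 0.079.
- Shift of 1.0 SE: P(Z > 0.96) + P(Z < −2.96) = 0.17.

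The nominal 5% two-sided error rate becomes about 8-17%. A separate calculation with 10 PHCs per arm agrees: a 5-point shift, equal to recoding about 9% of 'no' answers, raises the chance of a significant result favouring the intervention from 2.5% to about 14%.

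**Step 3. MACCI, ASHA-contact components only.** Full antenatal care, facility delivery, DPT3 and exclusive breastfeeding are not ASHA contact. Their weight is 2 × 0.0825 + 2 × 0.125 = 0.415. For the other five, using the weights in 5.1 and the Table 9 control values:

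| Component | Weight | 1 − control value | Product |
| --- | --- | --- | --- |
| Antenatal ASHA visits | 0.0825 | 0.35 | 0.029 |
| Complete HBNC | 0.25 | 0.95 | 0.238 |
| Care sought, newborn | 0.0825 | 0.73 | 0.060 |
| ORS from ASHA | 0.0825 | 0.35 | 0.029 |
| Care sought, ARI/fever | 0.0825 | 0.73 | 0.060 |
| Sum | | | 0.416 |

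Shift: 0.416 × 0.05 = 0.021; 0.416 × 0.10 = 0.042. That is 2.1-4.2 points, or 14-28% of the 15-point target.

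**The case against.** The strongest reply is that 6.1 is a single sentence in a design paragraph, that its reason plainly concerns providers and families, and that nothing in it says data handlers or the analyst will know the arm. Section 15.4 refers to a statistical analysis plan and 16.1 to cleaning protocols still to be prepared; neither is shown, and masking of the analyst often sits in the former. The edit controls are substantial, and 16.1 adds a paper record checked against the electronic one. This stands in part. A biased edit would leave a trail, and later documents may add masking. But a plan that masked the analyst would still have to be reconciled with the unqualified sentence in 6.1.

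A reader might also infer more than the protocol supports:
- That investigators decide the queries. Section 15.2 gives the first check, and clarification with collectors, to the data administrator; investigators share in cleaning.
- That one organisation both builds and delivers the intervention and judges it. SEWA Rural conducts the study and supplies the facilitators and helpline, but the software has a separate partner, the state health department leads implementation (20.3.3), and government ASHAs deliver the care (18.1).
- That masking would cost nothing. No cost is given, and some queries need a return to the household (16.1), which reveals the location.
- That the whole of the assumed shift would be removed. Part of it would arise at interview. Data collectors do house-to-house surveillance of the whole area (section 12) and may learn the arm.
- That all of MACCI is exposed. Applying the shift to the full 1 − 0.36 would give 3.2-6.4 points, but about 42% of the weight lies on components that are not ASHA contact.

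**Conclusion.** The point holds in a limited form. Section 6.1 makes a design decision that its stated reason does not support, and the protocol masks no step in the handling of mother-reported primary outcomes, although most central steps could be masked. This is neither evidence that bias will occur nor a claim that safeguards are missing.

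The figures of 2.7-5.4 points for the 46% outcome, with an error rate of about 8-17%, and 2.1-4.2 points for MACCI illustrate an assumed 5-10% recording of 'no' as 'yes' in one arm. They pool interview and editing effects, and the protocol offers no basis for dividing them. Masked central handling would remove only the part that arises in editing and analysis. The case for the change rests on its low cost, not on a demonstrated size of bias.

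**What to change.** Limit the sentence in 6.1 to providers and families. Add that central endline data review, edit decisions and primary analysis are done on records in which PHC, block and arm are replaced by codes, and that the codes are held until database lock by the AIIMS statistician, whom 6.1 already describes as independent of implementation. Bring 15.2 and 16.1 into line, so that whoever approves edits sees only the coded records.

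Where existing staffing allows, assign data collectors at endline to PHCs of both arms and keep them out of implementation meetings.

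The cost is protocol wording, a code list, a custodial task for the statistician, and possibly some extra travel. Masking will stay incomplete for interviews and for queries that require a return visit to the household, and the protocol should say so. The change has to be in place before endline data collection starts.
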